### Hypotheses

2.1

The hypotheses of the present study are listed below and are based on clinical experience as well as on the available scientific literature (Caes et al., 2021):

*H1:* Improvements in some neuropsychological domains (e.g., processing speed and executive functioning) will be observed between the pre- and post-transplant phases.

*H2:* Improvement in some parent- (or guardians-) and patient-reported outcomes (e.g., emotional-behavioral problems and personal adjustment) will be observed between the pre- and post-transplant phases.

*H3:* Patients under cardiac and lung transplantation will suffer poorer neuropsychological outcomes and more emotional-behavioral problems, both in the pre- and post-transplantation phase, than patients under kidney transplantation.

*H4:* Patients under hematopoietic transplantation will suffer poorer neuropsychological and more emotional-behavioral problems, both in the pre- and post-transplantation phase, than patients under solid organ transplantation.

*H5:* Older patients will show poorer therapeutic adherence levels than younger patients.

*H6:* Executive functioning will mediate the relationship between several patient-reported outcomes (e.g., pain, anxiety, depression and sleep disorders) and therapeutic adherence.

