### Variables and instruments

3.4

The variables measured in this project, the instruments used and the informants who will complete each measure are detailed below:

Socio-demographic (sex, age, patient’s level of studies, parents’ level of studies) and clinical variables (current pharmacological treatment—active substance and dose). These data will be collected with an initial survey created *ad hoc* for the present study.Processing speed. The Symbol Digit Modalities Test (SDMT) (Smith, 2002) will be administered to patients.Visual sustained attention/vigilance. The Kiddie Continuous Performance Test, second edition (K-CPT 2) (Conners, 2006) will be administered to children aged 4 to 7 years, and the Continuous Performance Test, third edition (CPT 3) (Conners, 2014) to children aged 8 and above. This test computes several scores, as follows: Detectability, Omissions, Commissions, Perseverations, Hit Reaction Time (HRT), HRT Standard Deviation, Variability, HRT Block Change and HRT Inter-Stimulus Interval Change.Immediate and delayed verbal memory. A Spanish test based on the California Verbal Learning Test will be administered to patients. Specifically, the Spain-Complutense Verbal Learning Test for Children (TAVECI) (Benedet et al., 2017) will be administered to children aged 3 to 16 years; and the version for older patients (TAVEC) (Benedet and Alejandre, 2014) will be applied to adolescents aged 16 to 18 years. This test allows calculating a wide range of scores regarding the verbal memory performance, and the following scores will be specifically used in this study: Immediate Recall, Short Delay Free Recall, Short Delay Cued Recall, Long Delay Free Recall, Long Delay Cued Recall, Long Delay Recognition, Semantic clustering strategies, Serial clustering strategies, False positives, and Discriminability.Semantic memory. The Vocabulary subtest of the Wechsler Intelligence Scale for Children, fifth edition (WISC-V) (Wechsler et al., 2015) will be administered to patients up to the age of 16.11 years, and the adult version, fourth edition (WAIS-IV) (Wechsler, 2012), will be applied to patients up to 18 years.Verbal working memory and cognitive flexibility. The Digit Span subtest of the WISC-V (Wechsler et al., 2015) or the WAIS-IV version (Wechsler, 2012) will be administered to patients. Three neurocognitive domain-specific scores will be considered from the three differentiated parts of the task (Forward, Backward, and Sequencing subscales), as well as the global score (Digit Span) as a measure of cognitive flexibility (Wechsler et al., 2015).Verbal fluency. The Verbal Fluency Test (TFV) (Portellano Pérez and Martínez Arias, 2020) will be administered to patients. This test calculates the following eight scores: Phonological fluency, Semantic fluency, Excluded-letter fluency, Total Fluency Index, Errors in phonological fluency, Errors in semantic fluency, Errors in excluded-letter fluency and Total errors.Ability to inhibit cognitive interference. The Stroop Colour Word Test (SCWT) (Golden, 2020) will be administered to patients. Four scores can be computed from this test, such as: the Word reading (W), the Colour naming (C), the Colour-word (CW) and Resistance to Interference.Visuo-constructive organizational ability and immediate and delayed visual memory. The Rey-Osterrieth Complex Figure (ROCF) test (Rey, 2003) will be applied to patients. This test generates four scores: a copy score (accuracy in terms of visual–spatial constructional ability), the time required to copy the figure, and two delayed-recall scores (at 3 and 30 min).Non-verbal Intelligence. The Test of Non-verbal Intelligence, fourth edition (TONI-4) (Brown et al., 2019), using both parallel forms (A and B), will be administered to patients.Ecological Executive Functioning. The Behavior Rating Inventory of Executive Function, second edition (BRIEF-2) (Maldonado-Belmonte et al., 2017), in its parent-reported version, will be completed by the patient’s parents (or legal guardians).Emotional and behavioral problems. The Behavioral Assessment System for Children and Adolescents, third edition (BASC-3) (Reynolds and Kamphaus, 2020) will be administered, both the parent-reported version, by the patient’s parents (or legal guardians), and the self-reported version, by the patient. This questionnaire covers the personal (e.g., adaptive skills, resiliency, externalizing, and internalizing problems) and interpersonal/social domains (e.g., school problems, relationships with parents, interpersonal relations) of each patient.Pain intensity and interference. The Brief Pain Inventory (BPI) (Badia et al., 2003) will be used as a self-reported measure by patients. This questionnaire includes questions (from 0 to 10 referring to the last seven days) covering two dimensions: pain intensity (worst and mildest pain in the week, average pain, and current pain), and pain interference (general activity, mood, walking, school, sleep, as well as enjoyment of life).Sleep problems. The PROMIS Pediatric Sleep Disturbances Short Form (Forrest et al., 2018) will be used as a self-reported questionnaire by patients. It is a 4-item questionnaire that assesses problems of sleep onset and maintenance in the last 7 days.Insomnia. The Adolescent Insomnia Questionnaire (AIQ) (Bromberg et al., 2020) will be used as a self-reported measure by patients. It is a 13-item questionnaire that covers three domains: Sleep Dissatisfaction and Impairments, Sleep Onset, and Sleep Maintenance.Adherence to treatment. The Simplified Medication Adherence Questionnaire (SMAQ) (Ortega Suárez et al., 2011) will be used to evaluate therapeutic adherence as a self-reported measure. Also, blood levels of the prescribed drugs (mainly immunosuppressants) will be used to objectively evaluate therapeutic adherence, which will be extracted from the clinical history of each patient.

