### Procedure

3.5

The fieldwork for this study will take place at La Paz University Hospital (Madrid, Spain) and it will be conducted by clinical psychologists trained in neuropsychological testing ([name] and [name]).

First of all, patients and their parents (or legal guardians) will be briefly informed about this study by medical/surgical professionals and, if they agree, they will be referred to the Psychiatry, Clinical Psychology and Mental Health Unit at the Children hospital. This Mental Health team will inform the patients and/or their legal guardians, in a more exhaustive manner, about the objectives of the present study. An initial screening will be carried out to examine compliance with the inclusion/exclusion criteria and, if so, they will be given the information and informed consent forms. After authorization and consent to participate in this study, they will be sent electronic links to complete the battery of questionnaires, in which they will be identified with an anonymous code in order to preserve their identity under the strictest confidentiality; and, subsequently, the neuropsychological testing will begin. The neuropsychological assessment will be carried out in person and individually with each patient; while the digitalised assessment will require 4 types of links across the different platforms, from REDCap (Harris et al., 2009), Hogrefe TEA Ediciones and Pearson Clinical, for the self- and parent/legal guardians-reported questionnaires. Post-transplant evaluations will take place at 4 weeks and 6 months after transplantation. In these two post-transplant phases, the same type of tests and questionnaires described in the previous phase will also be administered, although with a shorter battery at 4 weeks. At each stage of the neuropsychological evaluation, tests will be administered during a single session. Sessions during the pre-transplant and the 6-months follow-up phases will have a duration of approximately one and a half to maximum 2 h (including a 10-min break). Testing at 4 weeks after transplantation will be of a shorter duration, around 45 min. After each assessment, the clinical psychologists will enter the data into the project database.

This study follows a mixed-methods approach: a quantitative methodology following an observational cohort design, based on standardized tests and questionnaires; as well as a qualitative methodology, based on focus groups.

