On the one hand, the quantitative evaluations will take place in both pre- and post-transplantation phases. Specifically, the assessment in the pre-transplant phase will take place, when possible, within 0–6 months prior to the transplantation, as recommended by expert consensus (Kaustov et al., 2021). The post-transplantation phases will take place at 4 weeks and 6 months after the surgery.

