### Statistical analyses

3.6

The data will be processed primarily using the statistical software IBM SPSS Statistics 29, among others, and mainly the following analyses will be performed:

First, descriptive analyses will be carried out for all variables to identify possible errors or outliers in dataset. Then, zero order correlation analyses will be computed to determine the degree of association between variables; and partial correlation analyses will be conducted to examine its association excluding the effect of other confounding variables.

Additionally, as main statistical analysis, a mixed Analysis of Covariance will be performed to evaluate the main effects between groups (2 types of transplant: solid organ and haematopoietic) and within groups (time variable with 3 levels: pre-, post-transplantation at 4-weeks and 6-months follow-up) as well as potential interactive effects, excluding the effect of confounding variables. *P*-value adjustments for multiple comparison will be performed. In turn, other analytical strategies will be used to examine time series such as latent grow models. Finally, innovative statistical analyses based on multiple linear regression will be developed to examine the relative weight of the different predictor variables on the criterion variables, already published elsewhere (Fernández-Jiménez and Arnett, 2015).

All these statistical analyses will be complemented with the appropriate effect size indexes for each statistical test (e.g., *f*, omega-square and *R^2^* indexes) (Cohen, 1992). Additionally, Reliable Change Index (RCI) will be computed in order to determine the real change of each individual score between measurements over time (Kiselica et al., 2023).

Since the main statistical analysis in this study will be a mixed Analysis of Covariance (2 × 3), with a statistical power = 0.95 and a risk/significance level of alpha = 0.05, to detect at least a moderate effect size (*f* = 0.25) on the outcome variables included, a minimum sample size of 36 patients will be required according to GPower 3.1.9.4 software.

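### On the performance tests, H1 counts any pre-to-post gain as improvement, but the planned time effect cannot separate retest gain from real change, and no practice correction is stated for the RCI

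*Protocol article*

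**What the plan says.** All references are to the Protocol article.

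- **Hypothesis.** H1 (Hypotheses, 2.1) states that "Improvements in some neuropsychological domains (e.g., processing speed and executive functioning) will be observed between the pre- and post-transplant phases".
- **Repeat testing.** At the two post-transplant visits "the same type of tests and questionnaires described in the previous phase will also be administered, although with a shorter battery at 4 weeks" (Procedure, 3.5). The figure listing the instruments per phase is not shown, so which tests are given three times and which twice cannot be read from the text.
- **Timing.** The pre-transplant assessment "will take place, when possible, within 0–6 months prior to the transplantation" (Procedure, 3.5).
- **Group analysis.** The main analysis is a 2 x 3 mixed ANCOVA (Statistical analyses, 3.6). Its between-patient factor is solid organ versus haematopoietic transplant, and its within-patient factor is the "time variable with 3 levels: pre-, post-transplantation at 4-weeks and 6-months follow-up". Confounders are to be adjusted for, and p-values corrected for multiple comparisons by a method not named.
- **Individual analysis.** The "Reliable Change Index (RCI) will be computed in order to determine the real change of each individual score between measurements over time" (Statistical analyses, 3.6). A source is cited, but no variant, cut-off or practice term is given.
- **Alternate forms.** TONI-4, "using both parallel forms (A and B), will be administered to patients" (Variables and instruments, 3.4), is the only instrument with parallel forms named.
- **Limitations.** The Discussion lists sampling, the observational design, small organ subgroups, untested domains and attrition. Practice or retest effects are not mentioned.

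**The concern.** Scores on speeded, memory and executive performance tests can rise on a second sitting because the child has met the task before. To tell this from real change, a plan needs a retested comparison group that has not been transplanted, alternate forms, or an external estimate of the expected retest gain. The article states none of these for the performance tests closest to H1's own examples: symbol-digit, Stroop, verbal fluency and Digit Span.

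The error runs in one direction. It favours H1, because a mean retest gain enters the time effect as apparent improvement. It works against the objective of identifying possible peri-surgical neurocognitive disorders (Objectives, 2), because the same gain offsets true decline in each child. The Introduction and Discussion tie early detection to educational adaptation and rehabilitation, so a masked decline has a practical cost.

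**Working it through.** **1. The plan's own figure.** The stated minimum of 36 patients (f = 0.25, alpha 0.05, power 0.95) was checked with noncentrality f² x N x m/(1 - rho), m = 3 times and 2 groups. It is reproduced for the within-patient effects with a correlation among repeated measures of about 0.60, which the text does not state. With 0.50, 44 patients are needed and 36 give power 0.906. This has no bearing on the present point. The values 36 and the planned 60 (Selection of participants, 3.2) are used below as numbers of complete pairs.

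**2. Exposure.** With baseline 0-6 months before transplant, a test in the 4-week battery is repeated about 1-7 months after first exposure. A test given only at 6 months is repeated 6-12 months after it.

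**3. What the time effect estimates.** For any performance test, mean observed change = mean real change + mean retest gain. Both ANCOVA groups are transplanted and retested, so neither isolates the second term. Covariate adjustment does not remove a shift common to all children. A multiplicity correction raises the threshold but leaves the shift in place.

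**4. Group-level illustration.** The documents give neither the practice gain d (in SD units) nor the retest correlation r, so both are assumed. With zero true change, a paired two-sided 5% test has dz = d/sqrt(2(1 - r)) and noncentrality dz x sqrt(N). Example: d = 0.2, r = 0.7 gives dz = 0.2/0.775 = 0.258. At N = 60 the noncentrality is 2.00 and the probability of significance is 0.503.

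| d | r | N = 36 | N = 60 |
|---|---|---|---|
| 0.1 | 0.7 | 12% | 17% |
| 0.1 | 0.8 | 15% | 23% |
| 0.2 | 0.7 | 33% | 50% |
| 0.2 | 0.8 | 45% | 67% |
| 0.3 | 0.7 | 62% | 84% |
| 0.3 | 0.8 | 79% | 95% |
| 0.4 | 0.7 | 85% | 98% |
| 0.4 | 0.8 | 96% | 99.8% |

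The nominal rate is 5%. If ten comparisons were Bonferroni-corrected (alpha 0.005 each, an assumed example), the range for d = 0.2-0.4 would be 9-78% at N = 36 and 19-97% at N = 60.

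**5. Individual-level illustration, if the RCI has no practice term.** Assume reliability 0.8, d = 0.3 and cut-off ±1.96. The SE of the difference is sqrt(2 x 0.2) = 0.632 SD.

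- No true change, flagged improved: 1 - Phi(1.96 - 0.3/0.632) = 6.9%, against 2.5% nominal.
- No true change, flagged declined: Phi(-1.96 - 0.3/0.632) = 0.7%, against 2.5%.
- True 1-SD decline detected, practice removed: Phi(-1.96 + 1/0.632) = 35%.
- True 1-SD decline detected, practice left in: Phi(-1.96 + 0.7/0.632) = 20%.

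With a ±1.645 cut-off, false improvement is 12.1% (nominal 5%) and detection falls from 47.5% to 29.5%.

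**The case against.** **The RCI variant is unknown.** A reader might infer that an uncorrected RCI is planned. The text does not say so: it names no variant, practice-adjusted versions exist, and the cited source is not at hand. This stands. The RCI figures are therefore conditional, and the variant could be fixed in a fuller document. It does not rescue H1, because an adjusted RCI leaves the group-level time effect uncorrected.

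**The schedule may be lighter than it looks.** A reader might infer that every performance test is repeated at all three visits, within weeks. The shorter 4-week battery (about 45 minutes) and the missing figure do not support that. Some tests may be given only twice, 6-12 months apart. This stands too, but two exposures are enough for a retest gain.

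**Growth in raw scores.** A reader might also infer that normal development inflates the scores. The article is silent on score metric, which a condensed article may leave out, and it describes standardised tests with age-specific versions. That reading is not supported. Age-norming would in any case remove maturation, not practice.

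**The limits are partly acknowledged.** The study is described as "a quantitative methodology following an observational cohort design", the Discussion disclaims causal inference, and H1 speaks of what will be observed, not of its cause. That caveat concerns why ability changed. It does not warn that a score gain may not be a gain in ability at all.

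**The magnitude depends on chosen inputs.** This stands. The group-level rates come from one unadjusted paired test, not the planned ANCOVA, and they fall at small d or after multiplicity correction. They stay above the nominal rate in every case shown.

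**Conclusion.** The point holds for the performance tests. As written, the plan counts mean retest gain as support for H1, and it states nothing that would keep that gain from masking decline. It does not reach the parent-rated BRIEF-2 or the questionnaires, and TONI-4 is less exposed because it has parallel forms. The solid organ versus haematopoietic comparison (H4) and the group-by-time interaction are less affected if practice is similar in both groups.

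The direction follows from the design. The size does not: it rests on the assumed practice gain, retest correlation and RCI cut-off, and it ranges from a modest excess over 5% at 0.1 SD to near-certain significance at 0.4 SD with 60 patients. The documents do not show that H1 will be falsely confirmed. They show that a confirmed H1 could not be read as improvement on these tests.

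**What to change.** - **Statistical analyses (3.6), individual change.** Specify a practice-corrected or regression-based RCI using published retest data where available, and state its cut-off.
- **Statistical analyses (3.6), group change.** For each performance test, compare the mean time effect with the expected retest gain instead of zero.
- **Hypotheses (2.1).** Word H1, for performance tests, as gain beyond the expected retest gain.
- **Tests without suitable retest data.** State that a mean gain on that test will not be interpreted as improvement.
- **Discussion (4).** List retest effects among the limitations.

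The cost is analysis wording and a search for retest data, with no extra testing. Some tests will support a narrower conclusion. Published retest intervals and samples may not match these children, so the correction is approximate, and over-correction could produce apparent decline.

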## Methods and analysis

3

### Study design

3.1

This project follows a mixed-methods approach, hence the present study protocol will follow the SPIRIT 2013 guidelines (Chan et al., 2013) adapted to the STROBE statement (von Elm et al., 2007), for the observational study; and to the COREQ statement (Tong et al., 2007), for the qualitative study (focus groups).

### Selection of participants

3.2

The potential participants will be all those children and adolescents already included (or in the imminent phase of being included) in the waiting list for a transplant of any solid organ (single or combined), or allogeneic hematopoietic from La Paz University Hospital (Madrid, Spain). The estimated sample size was 60 patients (for any type of transplant, organ, or hematopoietic). Recruitment will last from November 1, 2022, until June 2024.

For this purpose, a non-probabilistic technique of incidental sampling (or purposive sampling technique) will be used in this study according to the following inclusion and exclusion criteria listed below, based on other related studies:

#### Inclusion criteria

3.2.1

Age between 6 and 18 years.Females and males.Spanish as mother tongue or a very high level of Spanish to understand their participation in the study as well as to be able to complete the measurement instruments.

#### Exclusion criteria

3.2.2

Diagnosis of an autism spectrum disorder, severe sensory/motor limitations, or acquired brain damage.Presence of a severe uncontrolled comorbid disease, independent of the disease motivating the transplant.

### Ethical considerations

3.3

Firstly, this study will be carried out in accordance with the principles established in the Helsinki declaration, strictly respecting confidentiality and the requirements of Spanish (14/2007, of July 3, 2007, on Biomedical Research; and Organic Law 3/2018, of December 5, 2018) and European data protection regulations.

Secondly, all those legally responsible for the patients will receive an information sheet about the study, will be able to resolve their questions about the study and will freely give their informed consent so that minor patients can participate in the present study. It will be emphasized at all times that participation in this research is completely voluntary and that refusal to participate in the study will not have any unfavorable repercussions for the patient in their care process, neither will abandoning the study at any given phase. In those cases in which the parents of the patient are divorced and there is no way of obtaining consent from both of them, the participation of the minor in this research will be rejected.

Clinical data will be kept separate from identification data, and the databases will be encrypted and stored on computers used exclusively for this project. All records will be maintained in compliance with the precepts established in current legislation on the protection of personal data (Organic Law 3/2018, of December 5, 2018). The persons responsible for processing the research data will only do so in accordance with the purpose stated on the informed consent form. Once the purpose of this study is accomplished, all personal data will be destroyed, as will any documentary support containing the personal data incorporated into the study.

This study was approved by the Research Ethics Committee of La Paz University Hospital (Madrid, Spain).

